# The ADEM2 project: early pathogenic mechanisms of preschool wheeze and a randomised controlled trial assessing the gain in health and cost-effectiveness by application of the breath test for the diagnosis of asthma in wheezing preschool children

**DOI:** 10.1186/s12889-023-15465-6

**Published:** 2023-04-03

**Keywords:** Asthma, Preschool, Wheeze, Diagnosis, Exhaled VOC, Breath test, Biomarkers, Pathogenesis

## Abstract

**Background:**

The prevalence of asthma-like symptoms in preschool children is high. Despite numerous efforts, there still is no clinically available diagnostic tool to discriminate asthmatic children from children with transient wheeze at preschool age. This leads to potential overtreatment of children outgrowing their symptoms, and to potential undertreatment of children who turn out to have asthma. Our research group developed a breath test (using GC-tof–MS for VOC-analysis in exhaled breath) that is able to predict a diagnosis of asthma at preschool age. The ADEM2 study assesses the improvement in health gain and costs of care with the application of this breath test in wheezing preschool children.

**Methods:**

This study is a combination of a multi-centre, parallel group, two arm, randomised controlled trial and a multi-centre longitudinal observational cohort study. The preschool children randomised into the treatment arm of the RCT receive a probability diagnosis (and corresponding treatment recommendations) of either asthma or transient wheeze based on the exhaled breath test. Children in the usual care arm do not receive a probability diagnosis. Participants are longitudinally followed up until the age of 6 years. The primary outcome is disease control after 1 and 2 years of follow-up. Participants of the RCT, together with a group of healthy preschool children, also contribute to the parallel observational cohort study developed to assess the validity of alternative VOC-sensing techniques and to explore numerous other potential discriminating biological parameters (such as allergic sensitisation, immunological markers, epigenetics, transcriptomics, microbiomics) and the subsequent identification of underlying disease pathways and relation to the discriminative VOCs in exhaled breath.

**Discussion:**

The potential societal and clinical impact of the diagnostic tool for wheezing preschool children is substantial. By means of the breath test, it will become possible to deliver customized and high qualitative care to the large group of vulnerable preschool children with asthma-like symptoms. By applying a multi-omics approach to an extensive set of biological parameters we aim to explore (new) pathogenic mechanisms in the early development of asthma, creating potentially interesting targets for the development of new therapies.

**Trial registration:**

Netherlands Trial Register, NL7336, Date registered 11–10-2018.

## Background

Respiratory symptoms, such as wheeze, breathlessness, chronic cough, and sputum production, are very common in young children. Around 40% of all children under the age of 6 suffer from these asthma-like symptoms [1, 2]. Although asthma is the most prevalent chronic disease in children, only the minority (around 30%) of preschool children with recurrent wheeze have persistent wheeze and asthma in later life [1–3]. The majority of wheezing preschool children has transient, viral infection-induced symptoms without an increased risk for asthma and most of the time no need for asthma medication (so called ‘transient wheeze’ or ‘viral wheeze’). At present, there is no proper clinical instrument available that can discriminate between ‘persistent wheeze’ (children with asthma) and ‘transient wheeze’ (children without asthma) at preschool age.

### Prediction of asthma in the guidelines

The prediction of asthma in preschool children with asthma-like symptoms (such as wheeze) has been an important unresolved topic. A reliable asthma diagnosis in preschool wheeze is not possible, as noted by the various (inter)national asthma guidelines [4–7]. These guidelines state that a probability diagnosis based on symptom patterns combined with a careful clinical assessment of family history and physical findings has low positive predictive value. Thus, appropriate treatment and clinical decision-making is hampered in wheezing preschool children.

### Wheezing phenotypes and clinical predictive indices

Whilst no tests diagnose asthma with certainty, various attempts were done to improve an asthma diagnosis in young children. For example, different phenotypes have been described based on triggers of wheeze obtained by clinical history, including episodic (viral) wheeze and multi-trigger wheeze. This was adopted by the European Respiratory Society (ERS) and American Thoracic Society (ATS) taskforce in 2008 [3]. However, accumulating evidence suggested that splitting preschool recurrent wheezing disorders into wheezing phenotypes is an oversimplification, with considerable overlap in symptoms and response to treatment, and is of limited clinical value [8]. Alternatively, clinical indices were developed to classify and predict development of asthma in young children with respiratory symptoms. Various prediction rules, mainly based on clinical parameters, have been developed. Amongst these prediction rules are the (modified) Asthma Predictive Index (API) [9], the Isle of Wright score [10], and the PIAMA risk score [11]. These indices are based on easily obtainable clinical variables. The (modified) API index is increasingly used and mentioned in various guidelines [4]. With the API, young children with a higher risk to develop asthma can be identified based on the age of onset and frequency of wheezing episodes combined with major criteria (parental history of asthma and eczema) and minor criteria (diagnosed allergic rhinitis, wheezing apart from colds, and eosinophilia). Unfortunately, in general the sensitivity of these predictive indices, is low to modest as is their clinical value [12–14]. Moreover, when external validation was performed, these predictive models had only low to modest predictive ability and generalizability (AUC range: 0.62–0.83) [15].

### Consequences of an absent diagnostic instrument for an early diagnosis in wheezing children

In current clinical practice, the absence of a proper diagnostic test for an early asthma diagnosis in young children leads to at least 2 major health problems: 1) children with asthma are frequently underdiagnosed and undertreated; 2) children with transient wheeze are often overtreated with asthma medication.

Considerable underdiagnosis and undertreatment occurs in young children with asthma [16]. Preschool children with asthma and more severe symptoms (having asthma-like symptoms more than twice per week) benefit from maintenance treatment with inhaled corticosteroids (ICS). This improves symptoms, lung function, quality of life, and reduces exacerbation rate and hospital admissions [1]. As a consequence of undertreatment, more children will suffer from uncontrolled asthma with more exacerbations, emergency care visits, hospital admissions, and in the long run even airway remodelling and permanent loss of lung function [17]. Therefore, this undertreatment may lead to reduced quality of life and increased direct and indirect medical costs.

Overtreatment of children with transient wheeze occurs with an increased risk of side effects of ICS and bronchodilators such as reduced linear growth, tremor, and palpitations [1, 16]. Treatment with bronchodilators or ICS might not be very effective in children with viral wheeze, which leads to preventable costs of care and preventable side-effects [1, 17, 18]. Moreover, because of uncertainty of the parents and the primary care physicians, a lot of children with transient wheeze are referred to secondary or tertiary care centres, with additional examinations such as chest X-rays, allergy tests, and treatment with asthma drugs as a consequence.

Therefore, a predictive instrument for an early asthma diagnosis will be of great importance to improve treatment of and care for the large group of young children with wheezing symptoms, and will probably lead to a substantial reduction in the cost of care.

### Volatile organic compounds

Over the past decades, exhaled breath has evolved as a new bodily matrix that has great potential for diagnostic and monitoring purposes [19, 20]. Various research groups demonstrated that exhaled compounds, such as volatile organic compounds (VOCs), can be the base of biomarkers to improve accurate diagnoses and management decisions in pulmonary diseases such as lung cancer and chronic obstructive pulmonary disease. VOCs are an assorted group of carbon-based chemicals that are volatile at room temperature. VOCs are omnipresent in ambient air and once inhaled they are exhaled again in unchanged or metabolised form. At the same time, certain VOCs are endogenously formed in the body during several (patho) physiological processes, such as inflammation, entering the blood stream and exhaled via the lungs [20]. Diseased organs may have a specific profile of VOCs in exhaled breath that distinguish them from healthy organs [19–21]. Although the field of exhaled breath analysis is rapidly growing, VOCs data in children with pulmonary diseases are still limited.

### A predictive breath test for asthma in preschool children

In 2015 we published the results of a longitudinal study in 202 wheezing children, in which we assessed the potential of exhaled breath biomarkers for a paediatric asthma diagnosis, called the ADEM study (Asthma DEtection and Monitoring study) [22]. In this study, we explored whether clinical parameters, genetic information, inflammatory markers in exhaled breath (such as VOCs), and early lung function measurements assessed at preschool age, could help to predict asthma at age 6 in wheezing preschool children. Our most important finding was that a reliable asthma diagnosis could be established in young children (sensitivity 84%, specificity 82%) by combining clinical information (such as family history of asthma, atopic status and symptoms), and a profile of exhaled VOCs [22]. The addition of 9 most predictive exhaled VOCs to a clinical predictive index, significantly improved an asthma diagnosis (AUC, 89%, an increase of 28% compared to using only the asthma predictive index (API)) which persisted in an external validation set. The chemical identity of these 9 VOCs was determined (see Table 1). This is a promising finding, which demonstrates the proof of principle that exhaled breath biomarkers can be used for an early asthma diagnosis.

**Table 1 Tab1:** the chemical identity of the 9 most predictive VOCs of the ADEM algorithm. BCa 95%CI: Bias Corrected accelerated 95% Confidence Interval [22]

Predicting VOC	Odds ratio	BCa 95% CI	p-value
Acetone	0.93	0.82 to 0.98	< 0.01
Octane	2.91	1.09 to 13.63	< 0.01
2-methylhexane	3.97	1.22 to 126.22	0.01
2,3,6-trimethyloctane	1.51	0.90 to 6.95	0.09
2,6,10-trimethyldodecane	0.98	0.94 to 0.99	0.01
2,4-dimethylpentane	0.79	0.58 to 0.99	0.03
2,4-dimethylheptane	4.25	2.29 to 42.44	< 0.01
2-undecenal	0.08	< 0.01 to 0.53	0.03
2-methylpentane	0.09	< 0.01 to 0.37	< 0.01

### VOCs-sensing techniques in daily clinical practice

In the ADEM study, we used gas chromatography–*time-of-flight*–mass spectrometry (GC-*tof–*MS) to measure exhaled VOCs [22]. Although GC–MS is the gold standard for the identification of VOCs, it is less suitable for clinical application as it is expensive, time consuming and requires extensive technical assistance. Recently, various promising techniques to measure exhaled VOCs such as sensor-based technologies, and selected ion flow tube mass spectrometry (SIFT-MS) technique became of interest [19, 20]. These techniques are cheaper, easier to handle, and provide fast results in comparison to GC–MS. For the application in clinical practice and the implementation in the health care system, a point-of-care breath test based on these faster and cheaper VOCs sensing techniques would be more appropriate.

### Pathophysiological mechanisms

Although the assessment of VOCs is attractive by the non-invasive nature, there is limited understanding of their origin in asthma. VOCs can be formed during various pathophysiological processes, such as airway inflammation and oxidative stress, induced by host and coexisting micro-organisms. Analysing the underlying mechanisms resulting in the formation of predictive exhaled biomarkers such as VOCs, may give insight in the underlying disease pathways leading to the early development of asthma [19, 20]. Understanding pathophysiological mechanisms is the key to improve early diagnosis, monitoring and treatment and maybe even secondary prevention of asthma development. For example, it was found that a disruption of the composition of gut and lung microbiota may be associated with asthma development and that a changed microbiome could be reflected in specific VOCs patterns in exhaled breath. However, the exact role of microbiota and its mechanisms in asthma development are still largely unknown. Also, in the ADEM study multiple genetic risk variants were found to be associated with the development of asthma at age 6 years. For example, there was an interaction between bacterial colonisation of the upper airways, genetic variants in the *TLR*s and *CD14* genes, and the development of asthma at age 6 years [23]. In the same cohort (and replicated in an independent birth cohort) a negative association of the CG/GG-genotype of rs528557 in the *ADAM33* gene with childhood asthma was found, confirming that genetic variation in the *ADAM33* gene may be implicated in the progression of wheeze into childhood asthma [24]. In an integrative genomic approach, data suggested that *ICAM-1* was likely to be involved in the development of childhood asthma [25]. Although these data provide valuable insight in the development of childhood asthma, the cumulative predictive power of genetic risk variants in polygenic risk scores is limited [26]. Additional layers of ‘omic’ data, such as epigenetics, may be more powerful as predictive biomarkers.[26] Epigenetics refers to DNA changes that regulate gene expression without altering the DNA sequence. A recent study showed the high diagnostic accuracy of nasal DNA methylation to diagnose allergic asthma in school aged children in a cross-sectional design [27]. Moreover, blood DNA-methylation at 14 CpG sites was associated with childhood asthma as early as the age of 4 years. These whole blood signatures were driven by large DNA-methylation differences within sorted eosinophils, which has promising diagnostic potential [28].

### Objectives of the new study: the ADEM2 study

The previous ADEM study generated a lot of insight in the diagnostic potential of VOC patterns in exhaled breath with respect to an early diagnosis of asthma, and in multiple potential underlying pathophysiological mechanisms leading to the development of asthma. However, since then, many new questions arose. For example with regards to the feasibility of bringing the assessment of VOCs in exhaled breath into daily clinical practice, and with respect to the impact an early diagnosis of asthma will have on wheezing preschool children and their parents. Also, recent developments in the evolving field of multi-omics generated new approaches to investigate the early pathogenesis of asthma. Therefore, a new randomised controlled trial and prospective study in wheezing preschool children was designed, the ADEM2 study.

The primary objective of the ADEM2 study is to prove health gain and reduction in costs by application of a point-of-care (POC) breath test for an early asthma diagnosis in preschool children. A multicentre randomised controlled trial (RCT) in 220 wheezing preschool children will be performed. Children will be randomised into an intervention group (*n* = 110) in which the doctors and parents will be informed about the predicted asthma diagnosis provided by the breath test, or into a usual care group (*n* = 110) in which all parties are masked for the predicted diagnosis. The second objective is to further develop and validate a reliable, non-invasive point-of-care breath test. In a prospective observational study we will assess feasibility, accuracy and reproducibility of the innovative VOC techniques (e.g. SIFT-MS and VOC sensors) in comparison with the gold standard breath test (GC-tof–MS), for an early asthma diagnosis in wheezing preschool children. The third and final objective of the ADEM2 project is to combine metabolomic, immunological, (epi)genomic, transcriptomic, and microbiome data to unravel potential important pathways for asthma development. Moreover, the utility of predictive, multi-omic testing of childhood asthma in wheezing pre-school children will be explored. This knowledge can offer clues for novel diagnostic tests and proper or even revised treatment (e.g. microbiota-based therapy) in wheezing children.

### Hypotheses of the ADEM2 study

The hypothesis of the clinical trial of the ADEM2 study is that application of the breath test in preschool children with asthma-like symptoms will result in important health gain and reduction of costs of care. In children with asthma, we expect that an early diagnosis by the breath test will result in more targeted and better treatment. This will facilitate better asthma control, improved lung function, less exacerbations, less hospital admissions, improved quality of life, and probably less airway remodelling. In children with transient wheeze, we hypothesise that an early diagnosis will diminish uncertainty of parents and treating doctors, with less referrals, less additional examinations (X-rays, allergy tests, microbial cultures or viral PCR tests), and less ineffective treatment (antibiotics, corticosteroids, or antihistamines). Parents will be reassured by the early diagnosis of transient wheeze, which will probably increase quality of life and decrease medical consumption. In both cases, cost savings are expected because of a proper diagnosis by the breath test due to significantly reduced hospital based care and medication use in children with transient wheeze, and prevention of undertreatment related sequela in children with asthma.

Our hypothesis of the observational cohort study with respect to the feasibility, reproducibility and accuracy of the alternative VOC-sensing techniques is that innovative techniques such as SIFT-MS are not inferior to the current golden standard GC–MS. We also hypothesise that new (combinations of) biomarkers will be found that improve the diagnostic accuracy to identify the wheezing preschool child developing asthma, such as epigenetic signatures of blood eosinophils, microbiome data of both nasopharyngeal swabs and faecal samples, whole RNA sequencing on blood, gene-expression of relevant asthma genes, and immunological markers.

## Methods

### Study design

The proposed study is a combination of a multi-centre, parallel group, two arm, randomised controlled trial and a multi-centre longitudinal observational cohort study. All children that participate in the RCT will also contribute to the observational cohort study.I

### Study setting

In order to achieve a good mixture of disease variability and severity in the study population (to maximise the external validity of the study results), the trial will be conducted in primary care practices and in the paediatric wards and outpatient departments of several general hospitals and university hospitals in the Netherlands. Preschool children aged 2 or 3 years will be recruited. The participating recruiting primary care practices are located in the southern and northern region of the Netherlands. The participating general hospitals are located throughout the country, as well as the participating university hospitals (Maastricht University Medical Centre, University Medical Centre Groningen, and Radboud University Medical Centre).

The healthy children that contribute to the observational cohort study will be recruited at day-care centres, via centres for youth health care, and by means of primary care practices, and (social) media.

### Eligibility criteria

The proposed study protocol includes both wheezing preschool children and healthy preschool children. In the RCT only wheezing preschool children will participate, whereas in the longitudinal cohort study both wheezing and healthy preschool children participate.

### Inclusion criteria

Wheezing children: age between 2 and 4 years old and presence of two or more objectified (by a physician or nurse) episodes of wheezing and shortness of breathHealthy children: age between 2 and 4 years old

### Exclusion criteria

Wheezing children: presence of chronic and/or inflammatory disease other than asthma (e.g. inflammatory bowel disease, auto-immune disorders, cardiac disease, congenital lung disease, kidney or liver disease), prematurity < 35 weeks gestational age, postnatal need for oxygen, CPAP, non-invasive or invasive ventilation, or mental disability.Healthy children: a history of asthma or wheeze, other chronic and/or inflammatory disease other than asthma (e.g. inflammatory bowel disease, auto-immune disorders, cardiac disease, congenital lung disease, kidney or liver disease), prematurity < 35 weeks gestational age, postnatal need for oxygen, CPAP, non-invasive or invasive ventilation or mental disability.

Children with a recent course of systemic corticosteroids or antibiotics are not excluded from participation, but the baseline visit will be postponed until at least one month after the treatment.

### Intervention

The intervention in the RCT consists of providing a probability diagnosis of either asthma or transient wheeze based on the earlier developed breath test of the ADEM study [22]. Based on this probability diagnosis, disease-specific recommendations on treatment and follow-up will be provided to the parents and treating physicians. At the start of the study, exhaled breath will be collected and sent to the central laboratory in the Maastricht UMC + for analysis on a GC-*tof*–MS. After analysis, the chromatogram is compared with our central database (based on the results of the ADEM study [22]) in order to determine whether the newly taken breath sample fits an asthmatic or a transient wheeze pattern of the selected VOCs. Parents and doctors of children allocated to the intervention group will receive the test result (probability diagnosis “asthma” or “transient wheeze”) within three months after the start of the study. In the children with a test result of “transient wheeze” in the intervention group, a restrictive policy towards use of asthma medication and referral to specialist care will be advised. In children with a test result of “asthma”, treatment with asthma medication according to international guidelines will be advised [29]. Parents and doctors of patients allocated to the usual care group will receive the test result at the end of the study at the age of 6 years. The management of preschool children with recurrent wheezing will be in accordance with national and international guidelines [29–31]. Both in the intervention and control group, treating doctors are at any time free to prescribe asthma medication, antibiotics or other drugs they judge as clinically necessary or meaningful.

### Outcomes

#### Randomised controlled trial

Primary outcome: difference between the intervention group and the usual care group in the percentage of well controlled asthma-like symptoms after 1- and 2-year follow-up. The percentage well controlled asthma-like symptoms will be based on the validated TRACK questionnaire.Secondary outcomes: differences after one year and at the end of the study between the intervention group and usual care group will be assessed with respect to:Number of exacerbationsLung function (spirometry) at 6 years of ageAirway resistance with forced oscillation techniqueQuality of life of children and their parentsPharmacotherapy (frequency and dosage of used medication)Growth velocity over 12, 24 and 36 months (cm/y), change in height SD scores over 12, 24 and 36 monthsPatient reported side-effects of medicationHealthcare resource use and –costs (standard and extra clinical visits, hospital admissions, referrals, laboratory tests, imaging tests)Costs outside healthcare (over-the-counter drugs)Absence of school and work (parents);

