### Sample size

*Randomised controlled trial* With a presumed percentage of well-controlled preschool children with asthma-like symptoms of 20% in the usual care group (based on reference [32, 33]), and of 40% in the intervention group, 91 patients in both groups are needed to detect this difference with an alpha of 0.05 and a power of 80%. Taking a dropout rate of 10% into account, we aim to include a total number of 220 preschool children with asthma-like symptoms.

*Prospective cohort study* For studies assessing the relationship between microbiome, transcriptomics, epigenetics, and atopic outcomes like asthma, a sample size of 70–80 is considered adequate [34, 35].

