**Randomised Controlled Trial**			
*Primary*			
Difference in the percentage of well controlled asthma-like symptoms after 1-year follow-up	I	TRACK-score	Unpaired t-test / Mann Whitney-U test
*Secondary*			
Pharmacotherapy	I, II, III, IV	Cumulative ICS dosage (fluticasone equivalent)	Mann Whitney-U test
Growth retardation	I, II, III, IV	SD deviation from target height	Unpaired t-test
Amount of exacerbations	I, II, III, IV	Amount	Chi-square test
Amount of hospital admissions	I, II, III, IV	Amount	Chi-square test
Quality of life child	I, II, III, IV	EQ-5-DY by proxy	Unpaired t-test / Mann Whitney-U test
Quality of life caretaker	I, II, III, IV	EQ-5-DY	Unpaired t-test / Mann Whitney-U test
Lung function (tremoflo)	I, II, III, IV	R_5_, R_5-20_, X_5_, X_5-20_, AX, F_res_ (baseline and % change after salbutamol)	Unpaired t-test / Mann Whitney-U test
Lung function (spirometry)	II, III, IV	FEV_1,_ FVC, MEF50 (baseline and % of change after salbutamol)	Unpaired t-test / Mann Whitney-U test
Absence of school and work (parents)	I, II, III, IV	Number of days	Chi-square test
Healthcare resource use and –costs	I, II, III, IV		Unpaired t-test / Mann Whitney-U test
Costs outside healthcare	I, II, III, IV	Euro	Unpaired t-test / Mann Whitney-U test
Cost-effectiveness	I, II, III, IV	Societal cost per QALY and health care cost per additional child with control of asthma-like symptoms	Sensitivity and bootstrap analysis

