### Assessment of improvement in health gain and costs of care with the application of the breath test in wheezing preschool children

The effect of the intervention will be assessed by comparing the outcome measures between the intervention and the usual care group in the RCT. Dichotomous parameters will be tested with the chi-square test. Continuous variables will be tested for significance with the unpaired t-test for normally distributed parameters and the Mann Whitney-U test in case of a not-normal distribution.

Total treatment costs will be calculated by multiplying resource use with the costs per unit. Resource use (visits to the general practitioner or specialist, emergency visits, hospital admission, lung function tests and other diagnostic procedures, the breath test, (over-the-counter) medication, and lost work days by parents due to sickness of the child) will be obtained from a specially designed questionnaire with a recall period of three months. The parents will fill out this questionnaire at baseline and at 3 months interval during the follow-up. Sources for valuation of the costs will be cost-prices of the Dutch manual for costing and cost-prices from the Dutch pharmacotherapeutic compass [45, 47–49] (reference data 2022). If necessary, local hospital cost-prices will be used, which are largely based on integral cost-prices from the Dutch hospitals [50]. Absence of work reported by the parents will be calculated by using the friction cost method, which is recommended by the Dutch manual for costing [47, 48].

The cost-effectiveness analysis from the healthcare perspective will be based on symptom control according to the TRACK questionnaire at 1 year follow-up (primary outcome measure). The cost-effectiveness analysis from the societal perspective will be based on the EQ-5D-Y. The EQ-5D-Y will be completed at baseline and at 3 months intervals during the follow-up, and will be filled out by one of the parents.

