A cost-effectiveness analysis will be performed from a societal and healthcare perspective with a time horizon of 2 years. Incremental cost-effectiveness ratios will be calculated as societal cost per QALY (societal perspective) and health care cost per additional child with control of asthma-like symptoms (healthcare perspective). Standard sensitivity- and bootstrap analysis will be performed to address uncertainty regarding costs and cost-effectiveness outcomes. Cost-effectiveness acceptability curves will be constructed reflecting the probability that the diagnostic breath test is cost-effective for a range of threshold values. Costs and effects after one year will be discounted at 4.0% and 1.5% respectively, according to the Dutch guidelines for health economic evaluation [45, 48].

All outcome parameters and corresponding outcome measures and methods of analysis are listed in Table 2. The large number of patients (*n* = 220) allows better representation of specific subgroups of specific age, background (primary or secondary/tertiary care), genetic predisposition, and geographic area. All these parameters will be measured and included in the multivariable analysis in order to assess possible influences on outcome. Intention-to-treat analyses will be applied. We will execute two subgroup analyses: one for age and one for level of care (first-line versus secondary/tertiary care). Two-sided *p*-values < 0.05 (with correction for multiple testing) will be regarded as statistical significant.

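### The protocol puts the primary outcome at 1 and 2 years in some places and at 1 year only in others, and gives no rule for a result that is positive at just one of them

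*Protocol article*

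**What the plan says.** Three places in the protocol article give two primary time points:

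- Abstract, Methods: "The primary outcome is disease control after 1 and 2 years of follow-up".
- Outcomes, Randomised controlled trial: "difference between the intervention group and the usual care group in the percentage of well controlled asthma-like symptoms after 1- and 2-year follow-up".
- The heading of the asthma-control analysis in the statistical methods, which repeats "percentage of well controlled asthma-like symptoms after 1- and 2-year follow-up".

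Two places give one:

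- Table 2, under Primary: "Difference in the percentage of well controlled asthma-like symptoms after 1-year follow-up". The text says that Table 2 lists every outcome parameter, yet control at 2 years has no row there, not even as a secondary outcome.
- The section on health gain and costs of care, which bases the healthcare-perspective analysis on "symptom control according to the TRACK questionnaire at 1 year follow-up (primary outcome measure".

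The Sample size section starts from a "presumed percentage of well-controlled preschool children with asthma-like symptoms of 20% in the usual care group" and 40% with the intervention, and concludes that "91 patients in both groups are needed to detect this difference with an alpha of 0.05 and a power of 80" per cent. It allows 10% dropout, aims for 220 children, and does not say at which time point the 20% and 40% apply. The section on health gain and costs sets the threshold at two-sided p < 0.05, "with correction for multiple testing) will be regarded as statistical significant". It does not say which tests the correction covers.

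**The concern.** The confirmatory hypothesis is not fixed. The text leaves open whether control at 2 years is co-primary, secondary or untested. If it is co-primary, the text does not say whether one success is enough or both are needed. If the trial is positive at 1 year and null at 2 years, or the reverse, the document supports more than one conclusion, and the favourable time point could be called primary after the data are seen. The risk is sharper because parents know the allocation (Allocation and blinding) and also complete the TRACK questionnaire (Questionnaires).

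The sample size adds to the problem. It spends the whole 0.05 on one comparison, so its stated power belongs to the single-time-point reading and has not been worked out for any two-time-point rule.

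**Working it through.** **Inputs from the document:** 20% v 40% controlled; two-sided alpha 0.05; power 80%; 91 per arm; 10% dropout; 220 in total, allocated 1:1 (110 per arm).

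**Assumptions, because the document gives no value:** the 20-point difference holds at both time points; the correlation ρ between the 1- and 2-year test statistics runs from 0 to 0.9; the proportions themselves are compared.

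**1. Reproduce the plan's figure.** The mean proportion is 0.30, so 2 × 0.30 × 0.70 = 0.42, and 0.20 × 0.80 + 0.40 × 0.60 = 0.40.

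n′ = (1.960 × √0.42 + 0.842 × √0.40)² / 0.20² = 81.2, or 82 per arm.

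With continuity correction, n = (n′/4) × (1 + √(1 + 4/(n′ × 0.20)))² = 90.9, or **91 per arm**.

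This matches exactly, so 91 is the number for one test at the full 0.05. Dropout: 91/0.90 gives 102 per arm. The planned 110 per arm therefore has some slack and leaves 110 × 0.90 = 99 evaluable.

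**2. One primary time point at 0.05.** Power = Φ[(0.20 − 1/n − z × √(0.42/n)) / √(0.40/n)]. The term 1/n is the continuity correction and is dropped for the uncorrected figure.

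- 91 per arm: 80.0% (uncorrected 84.3%).
- 99 per arm: 83.6% (uncorrected 87.3%).

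**3. Each time point at 0.025 (z = 2.241): power for one named time point.**

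- 91 per arm: Φ(0.554) = 71.0% (uncorrected 76.4%).
- 99 per arm: Φ(0.691) = 75.5% (uncorrected 80.2%).
- For 80% on the plan's own formula: 109 evaluable per arm. 109/0.90 gives 122 per arm, 244 in total. Without the continuity correction: 99 evaluable, so 110 per arm, which is the planned total.

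**4. Two time points, by success rule.** At ρ = 0 the uncorrected error is 1 − 0.95² = 9.75%. Power for at least one success is 2 × power − P(both); at ρ = 0 and 99 per arm this is 2 × 0.755 − 0.755² = 94.0%. The other rows use the bivariate normal distribution. Power is continuity-corrected, with uncorrected values in brackets in the last column.

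| ρ | Either suffices, each at 0.05: type I error | Either suffices, each at 0.025: power, 91 per arm | Same, 99 per arm | Both required, each at 0.05: power, 99 per arm |
|---|---|---|---|---|
| 0 | 9.75% | 91.6% | 94.0% | 69.9% (76.1%) |
| 0.5 | 9.07% | 85.1% | 88.3% | 73.8% (79.1%) |
| 0.7 | 8.35% | 81.8% | 85.4% | 76.0% (80.9%) |
| 0.9 | 7.04% | 77.2% | 81.1% | 79.2% (83.5%) |

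The answer depends on the success rule, and the document does not state one.

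**The case against.** A reader might infer that either the 5% error rate or the 80% power must fail. The documents do not support that, for four reasons.

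- If 1 year alone is primary, as Table 2 has it, neither fails.
- If both time points are required, type I error is not inflated and only power is in question.
- The protocol promises a correction for multiple testing, so an uncorrected error of 7% to 10% is not the stated plan. The method of correction may properly sit in an analysis plan that is not shown.
- The power loss depends on the rule. The 71% is for one named time point at 91 per arm. On the rule that creates the multiplicity, where either success counts, power at 0.025 each stays above 80% at 99 per arm throughout the range examined. The earlier ADEM study lost 2%. With a loss that low, about 107 per arm would remain, and power for a named time point would be 79.4% (83.5% uncorrected).

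Two further points are fair. The 1-year label in the economic section stands in a sentence about cost-effectiveness, so Table 2 is the main contrary text. Keeping both time points as primary, with a stated rule, would also be a valid design.

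All of this stands, and it limits the numerical consequences. It does not remove the contradiction: which time point is primary, and what counts as success, belong in the protocol, and its own sections disagree.

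**Conclusion.** The point holds as a contradiction about the primary time point and must be reconciled. The abstract, Outcomes and the asthma-control heading say 1 and 2 years; Table 2 and the economic section say 1 year. The sample size supports one test at 0.05 without saying when, and the scope of the promised correction is open.

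The statistical cost arises only if both time points are primary. It then depends on the rule:

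- **Either suffices, uncorrected:** type I error about 9.8% to 7.0%, which the promised correction disclaims.
- **Each at 0.025:** 75.5% power for a named time point at 99 per arm (80.2% uncorrected), but 94% to 81% for at least one success.
- **Both required at 0.05:** alpha kept, power about 70% to 79% at 99 per arm (76% to 84% uncorrected).

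The contradiction and the reproduction of 91 per arm rest on the text alone. The consequences rest on the assumed 20-point difference at both times, and the ranges also on the assumed correlations of 0 to 0.9.

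**What to change.** Name the proportion of children with a TRACK score of 80 or more at 1 year as the single primary endpoint, tested at two-sided 0.05. Table 2 and the economic section already use 1 year, and the sample size supports one such test. Say in Sample size that the 20% and 40% refer to 1 year. Test the 2-year proportion next in a fixed sequence, as the first key secondary endpoint, and give it a row in Table 2. Align the abstract, Outcomes and the asthma-control heading. State that the multiplicity correction does not apply to the single primary test.

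This costs wording only: no extra children and no loss of power at 1 year. The downside is that a confirmatory claim at 2 years becomes conditional on success at 1 year.

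If the sponsor prefers to keep both time points as primary, the protocol should state whether one or both must succeed and how alpha is split, and restate the power on that basis. For example, 80% power for each time point at 0.025 on the plan's own formula needs 109 evaluable and 122 randomised per arm.
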